#### Secondary outcomes

##### Sleep parameters based on actigraphy and sleep log

Sleep parameters from actigraphy and sleep log of our interest are total sleep time (TST), total time in bed (TIB), sleep onset latency (SOL), wake after sleep onset (WASO), napping, number of awakenings. Actigraphy measures sleep-wake rhythm from the presence or absence of wrist movement, by a nonintrusive wristwatch style device that patients will wear 24 h a day for 7 days [48]. This method yields typical sleep-pattern measures. This method has been widely used; reliability and validity have been established in children and adults [49–51]. A paper-pencil self-report sleep log containing a few items on sleep-wake schedule will be kept additionally measuring: in-bed and out-bed times, naps, and time not wearing actigraph (e.g., during showering). The actigraph that will be used in this study is the GTX3+, a commercially available valid, and reliable device for detecting sleep/wake diurnal patterns [52]. Accompanying standardized software ActiLife will be used to extract sleep outcomes with the Sadeh algorithm, developed for use in children as well as in young adults [53].

##### Circadian rhythm parameters—based on actigraphy

To obtain circadian rhythm parameters, a non-parametric analysis is performed on raw wrist-actigraphy data [54, 55]. Two parameters are calculated including (1) *Stability of circadian rhythm* indicated by intradaily stability (IS), which represents the similarity of day-night patterns over time by the strength of synchronization with environmental 24-h cues named zeitgebers. Stability of rhythm measured with IS ranges from 0 to 1, in which 1 is perfect synchronization with zeitgebers.

(2) *Fragmentation of circadian rhythm* is indicated by intradaily variability (IV), which is the amount of shifting between rest and activity. Ideally, a 24-h rhythm entails low fragmentation with a period of a daily activity as opposed to a period of rest at night. Fragmentation measured with IV ranges from 0 to 2, with a higher IV indicating a more fragmented rhythm.

##### Self-report questionnaires

*HR quality of life (HR-QoL)* will be assessed using the acute version of the Pediatric Quality of Life Inventory (PedsQL) Generic core scales (23 items). The multidimensional scales are physical, emotional, social, and school/work functioning. The 5-point Likert scale investigates to what extent the problem occurred in the last week. Each answer is reversed scored and rescaled to 0–100 scale (0 = low, 100 = high HR-QoL). The questionnaire demonstrates adequate reliability and validity in adolescents and Dutch references are available [56, 57].

*Fatigue* will be measured with the Checklist Individual Strength (CIS) subscale “fatigue severity” (8 items), scored on a 7-point Likert scale (range 8–56; higher score indicates more fatigue). CIS-F has shown adequate reliability and discriminative validity [58, 59] and has previously been used as a treatment outcome in online CBT studies in adolescents for fatigue [60, 61].

*Depressive and anxiety symptoms* will be assessed with the Hospital Anxiety and Depression Scale (HADS), measuring depressive (7 items, score range 0–21) and anxiety (7 items, score range 0–21) symptoms. Items are rated from 0 (no distress) to 3 (maximum). It has shown adequate psychometric properties in Dutch adult populations and in adolescents [62, 63].

*Perceived Cognitive Functioning* is assessed with the short form of the Peds-PCF. The Peds-PCF measures perceived neurocognitive functioning. The Dutch short form of the Peds-PCF has recently been tested through IRT modeling and showed satisfactory psychometric properties. Scores range from 10 to 50, in which a higher score indicates better neurocognitive functioning [64].

*Chronic distress* in the past 3 months will be measured using the Chronic Stress Questionnaire for Children and Adolescents (CSQ-CA). This 17-item self-report questionnaire has been validated in adolescents and has adequate psychometric properties [65]. It consists of 4-point Likert scales, 1 = not true for me at all to 4 = completely true for me (score range 17–68) in which a higher score indicates more distress in the past 3 months.

An *additional questionnaire* assesses subjective pain (on a 10-point visual analog scale (VAS)) and sleep medication use at T3, T6, and T12. Use of sleep medication, either prescribed or over the counter, is measured with a sleep medication 4-Likert scale item: “During the past month, how often have you taken medicine (prescribed or “over the counter”) to help you sleep?” (0 = not in the past month, 4 = three or more times in the past month). Furthermore, sociodemographic and clinical variables are derived from the national screening prior to the MICADO-study.

*Post-treatment intervention feedback* and *satisfaction with i-Sleep* will be evaluated after completing the intervention with a similar acceptability procedure as in the previous i-Sleep trial in breast cancer patients by Dozeman and colleges [38] existing of a 20-item satisfaction questionnaire developed by our research group. In addition, data will be extracted from the e-health platform to evaluate adherence, and acceptability by evaluating intervention feedback per session. These two questions are included at the end of each session: “How do you evaluate the session?” (1–10) and “Did this session help you” (1–10).

### Sample size calculation

The sample size calculation for the RCT is based on the comparison of sleep efficiency (SE) between the *iCBT-I* group and waiting list group after 3 months (T3) using the program PASS version 16. Previous studies have shown an improvement in SE varying between 4.3 and 11%, with a standard deviation of about 11.5%. In adults that received the i-Sleep intervention, baseline SE was around 67% [40]. Mean iCBT-I improvements in SE vary between 5 and 11% [31, 40]. Standard deviations were similar pre- and post-intervention, about 11.5% [40]. In this study, sample sizes of 29 in each group will achieve 80% power with a significance level of 0.05, a slope of *λ*^1^ = 8.0, with a standard deviation of *σ*^*y*^ = 11.5, and a standard deviation of the condition of *σ*^*x*^ = 0.50 using linear regression sample size calculation. Adjustment for the baseline score was not possible due to limited literature [66]. Previous studies show an average drop-out after treatment of 20% [39, 40, 67, 68]. Taking into account this potential drop-out rate of 20%, a total sample of 70 (35 per group) is necessary to achieve adequate power for the per-protocol effectiveness analysis.

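### The sample size calculation enters what reads as a within-group SD of 11.5 as the overall outcome SD; for the unadjusted comparison described, 29 per arm then gives about 74% power, not 80%

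*Protocol article*

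**What the plan says.** The section on sample size calculation in the protocol article bases the trial on the difference in actigraphic sleep efficiency (SE) between arms at 3 months. It gives the origin of the SD as earlier studies: "Standard deviations were similar pre- and post-intervention, about 11.5" per cent. A linear-regression routine is then run with a slope of 8.0, "with a standard deviation of *σ*^*y*^ = 11.5", and an SD of the condition indicator of 0.50. The result is: "In this study, sample sizes of 29 in each group will achieve 80% power with a significance level of 0.05".

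The same section says of the baseline measurement: "Adjustment for the baseline score was not possible due to limited literature". It adds 20% for drop-out and arrives at 35 per group, 70 in total. The section on statistical analyses plans a linear regression of SE at T3 that does adjust for the baseline score.

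**The concern.** In a regression sample size routine, σy is the SD of the outcome over all participants in both arms. It includes the spread that the treatment difference creates. The routine subtracts that part, slope² × σx², to obtain the residual variance.

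An SD that is about the same before and after treatment cannot be such a quantity in the ordinary reading: before treatment there is no treatment difference to include. If 11.5 is a within-group SD, it is already the residual SD, and the routine removes a treatment component that was never in it. The noise is then too small and the standardised effect too large.

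This is the only power statement in the article, and it supports one of the two primary outcomes.

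**Working it through.** **Inputs, all from the sample size section:** difference 8.0 points; SD 11.5; σx = 0.50; α = 0.05; 29 evaluable per arm. The article does not state sidedness; two-sided is assumed.

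**1. Reproduce the stated figure, with 11.5 as the overall SD.**
- Residual variance = σy² − (slope × σx)² = 132.25 − (8 × 0.5)² = 132.25 − 16 = 116.25.
- Residual SD = √116.25 = 10.78; standardised effect = 8/10.78 = 0.742.
- Noncentrality at 29 per arm = 8 / (10.78 × √(2/29)) = 2.825.
- Power = 79.3% (noncentral t, 56 df) or 80.7% (normal approximation).
- Normal-approximation n = 2 × (1.960 + 0.842)² × 116.25/64 = 28.5, so 29 per arm. The noncentral t needs 30.

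The stated 29 per arm and 80% are matched to within the choice of approximation.

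**2. Repeat with 11.5 as the within-group (residual) SD.**
- Standardised effect = 8/11.5 = 0.696.
- Noncentrality at 29 per arm = 8 / (11.5 × √(2/29)) = 2.649.
- Power = 74.0% (noncentral t) or 75.5% (normal approximation).
- Normal-approximation n = 2 × (1.960 + 0.842)² × 132.25/64 = 32.4, so 33 per arm. The noncentral t gives 79.5% at 33 and 80.7% at 34.

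**3. Consistency of the inputs.** If the within-group SD is 11.5 and the arms differ by 8, the overall SD at T3 is √(132.25 + 16) = 12.18, not 11.5.

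**4. Could a one-sided test explain the figure?** With SD 11.5 and one-sided 0.05, 29 per arm gives 83% to 84%, and 80% needs only 26 to 27 per arm. This does not reproduce the stated pair.

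**5. A separate point on drop-out.** 35 × 0.8 = 28 evaluable per arm, not 29. With SD 11.5 and no adjustment, 28 per arm gives 72.5%. The step from 74.0% to 72.5% comes from the drop-out allowance, not from the SD.

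**6. Baseline adjustment.** The residual SD becomes 11.5 × √(1 − r²), with r the correlation between baseline and T3. The article gives no r, so these values are assumptions (noncentral t):

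| r | Residual SD | Power, 29 per arm | Power, 28 per arm |
|---|---|---|---|
| 0.3 | 10.97 | 77.9% | 76.4% |
| 0.4 | 10.54 | 81.1% | 79.7% |
| 0.5 | 9.96 | 85.2% | 83.9% |
| 0.6 | 9.20 | 90.2% | 89.2% |

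Power of 80% is reached at r of about 0.37 with 29 per arm, and at about 0.41 with 28 per arm.

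**The case against.** Four points can be made for the plan.

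- **The sum is right for the inputs as labelled.** This stands. The stated figure reproduces, so the fault lies in which SD was put in the σy slot and not in the arithmetic that follows.
- **The article never calls the SD within-group, and the cited study is not at hand.** This stands as a limit. The reading rests on the remark that the SD was similar before and after treatment. It is a strong inference, because a pre-treatment SD holds no treatment difference, but it is an inference. For the same reason one cannot say that no source supports a residual SD of 10.78.
- **The inputs are rough.** At 29 per arm and a difference of 8, a residual SD of 10.5 gives 81.4%, 11.0 gives 77.7% and 12.0 gives 70.4%. At SD 11.5, a difference of 6 gives 50% and 9 gives 83%. The loss of 5 to 6 points is modest beside this. Rough inputs still do not justify moving one of them in the favourable direction without a reason.
- **The planned model is more efficient than the one in the calculation.** This stands and limits the consequence. A reader might infer from the 74% that the primary analysis is underpowered. The article does not support that: 74% belongs to an unadjusted comparison, the analysis adjusts for baseline, and a moderate correlation would restore 80%. Equally, no correlation is given, so adequate power is not shown either.

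**Conclusion.** The point holds for the calculation as the article describes it. If 11.5 is a within-group SD, the test is two-sided and there is no baseline adjustment, then 29 per arm has about 74% power (75.5% by normal approximation) against the stated 80%, and 80% needs 33 to 34 evaluable per arm. The type II error is then about 26% instead of 20%.

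Whether the baseline-adjusted primary analysis falls short is open. It depends on a correlation that the article does not give; about 0.4 would be enough with 70 randomised and 20% lost.

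**What to change.** Rewrite the sample size paragraph as follows.

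1. Enter 11.5 as the residual SD (equivalently, σy = 12.18 with slope 8.0 and σx = 0.50), and state unadjusted power of about 74% at 29 per arm. If the source shows that 11.5 really is an SD over both arms at T3, say so and keep the figure.
2. Separately, state that 35 per arm less 20% leaves 28, with unadjusted power of about 72.5%.
3. Report power for the baseline-adjusted model over assumed correlations. At 28 per arm: 76% at r = 0.3, 80% at 0.4, 84% at 0.5 and 89% at 0.6. State that the correlation is an assumption and that about 0.4 is needed for 80% with n = 70.

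The cost is one paragraph. The sample size and the analysis model stay as they are; the unadjusted power will look less favourable than the figure now printed.

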### Statistical analyses

Intention-to-treat as well as per-protocol analysis will be performed. A linear regression model adjusted for baseline score will be estimated to answer our primary study aim: the effectiveness of iCBT-I on SE and insomnia severity (ISI-score) in the iCBT-I group and the WL posttreatment (T3). The differences in SE and ISI at T3 between both groups will also be expressed in Cohen’s d effect sizes. For our secondary study aims, the clinical relevant response from the intervention effect posttreatment will be investigated by estimating a logistic regression model using yes/no clinical improvement based on the self-reported insomnia severity, since this represents both sleep problems, as daytime consequences of insomnia. A clinically relevant improvement is defined based on the self-report ISI as a decrease of ≤ 8 points between T0 and T3 [46, 67]. Due to the presence of repeated measurements a mixed linear model will be estimated to investigate the long-term effects. Mediation analyses at T3 are performed with the regression-based PROCESS macro [69] in which the potential mediational effect of chronic stress and napping on treatment effectivity on SE and ISI at T3 is tested. Missing data will be imputed under the appropriate missing data analysis assumptions, e.g. leading to multiple missing data imputation [70]. All analyses will be performed using SPSS and R.

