### Participants: inclusion and exclusion criteria

Patients are eligible when they fulfill the following criteria: have insomnia symptoms of at least subthreshold clinical severity (Insomnia Severity Index-score ≥ 8; ISI, see the “Outcomes” section), aged between 12 and 30 years old, diagnosed with (childhood) cancer or a low-grade brain tumor and at least 6 months since their last cancer treatment (since insomnia during treatment can be directly related to therapy and recover spontaneously). Exclusion criteria are (a) receiving palliative therapy; (b) not sufficiently fluent in Dutch; (c) significant cognitive impairment; (d) comorbidities that affect sleep or can be exacerbated by the sleep restriction in CBT-I, e.g., severely diminished eye-sight (sleep-wake rhythm can be affected due to poor sight), acute schizophrenia or substance abuse, history of a seizure disorder diagnosis or having experienced a seizure within the past 12 months; (e) pregnancy or patients who just had a newborn < 6 months, since sleep problems often occur in pregnancy and parents of a newborn; (f) shift work employment; (g) suicidality; (h) current psychological treatment for psychopathology (e.g., substance abuse, psychosis) or sleeping disorders; and (i) severe sleep disorders other than insomnia and untreated sleep-breathing disorders (SBD). Patients that use sleep medication such as benzodiazepines and melatonin will not be excluded since they may still benefit from the intervention. The use of sleep medication will, however, be monitored throughout the study, as a secondary outcome of the intervention.

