##### Insomnia severity—self-report questionnaire

*Insomnia severity* is additionally a primary outcome and will be evaluated using the Insomnia Severity Index (ISI) [46]. The ISI is a 7-item self-report questionnaire that assesses the nature, severity, and impact of insomnia. The dimensions are severity of sleep onset, sleep maintenance and early morning waking problems, sleep dissatisfaction, interference of sleep difficulties with daytime functioning, noticeability of sleep problems by others, and distress caused by sleep difficulties. It is rated on a 5-point Likert scale (total score 0–28). A score of 0–7 indicates absence of insomnia, 8–14 sub-threshold insomnia, 15–21 moderate insomnia, and 22–28 severe insomnia. Internal consistency is excellent in community as well as clinical samples (Cronbach’s alpha 0.90–0.91). Acceptable reliability is shown in cancer survivors [47]. A decrease of 8 points is considered a relevant clinical change in insomnia severity [46].

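### The ISI responder rule is reversed: a fall of at most 8 points counts as clinically relevant improvement, so larger falls count as failure

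*Protocol article*

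**What the plan says.** The Statistical analyses section of the protocol article addresses clinically relevant response as a secondary aim, by "estimating a logistic regression model using yes/no clinical improvement based on the self-reported insomnia severity". It then gives the coding rule: "A clinically relevant improvement is defined based on the self-report ISI as a decrease of ≤ 8 points between T0 and T3".

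The outcome section on insomnia severity, citing the same source for the 8-point figure, says: "A decrease of 8 points is considered a relevant clinical change in insomnia severity". It also fixes the direction of the scale: "A score of 0–7 indicates absence of insomnia, 8–14 sub-threshold insomnia, 15–21 moderate insomnia, and 22–28 severe insomnia". The total runs from 0 to 28.

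Participants may enter with an ISI as low as 8 (section on inclusion and exclusion criteria). Table 1 shows that the T0 value of the ISI is the one taken at screening.

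**The concern.** The ISI rises with severity, so a larger fall is a larger improvement, and a responder rule should set a minimum fall. The written rule sets a maximum. It admits participants who barely changed and excludes those who improved most.

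This logistic model is the only analysis in the article that asks whether individual participants improved by a clinically relevant amount. If it is coded as written, a beneficial intervention appears harmful on that question. If an analyst quietly reverses the sign instead, the analysis departs from the published definition, and a reader cannot tell a correction from a choice made after seeing the data.

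**Working it through.** The article reports no responder rate or odds ratio, so there is no stated figure to reproduce. The check has three parts.

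**1. Apply both rules to possible falls.** Let D = ISI at T0 minus ISI at T3, so that positive D is improvement.

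| D | As written (D ≤ 8) | Minimum fall (D ≥ 8) |
|---|---|---|
| −5 (worse) | improved* | not improved |
| 0 | improved* | not improved |
| 1 | improved | not improved |
| 7 | improved | not improved |
| 8 | improved | improved |
| 9 | not improved | improved |
| 15 | not improved | improved |
| 28 | not improved | improved |

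*If no change or a worsening is coded as a zero or negative decrease; the wording does not exclude this.

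The two rules agree only at exactly 8 points. A participant who enters at ISI 8 can fall by at most 8 − 0 = 8, so on that coding the written rule classes this person as improved whatever the T3 score.

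**2. Direction of the odds ratio.** ISI totals are whole numbers, so P(D ≤ 8) = 1 − P(D ≥ 9). The written outcome is the exact complement of a fall of at least 9 points, and its odds ratio is the reciprocal of the odds ratio for D ≥ 9. Any benefit that moves more participants past 8 points lowers the written response rate in the intervention arm and puts the odds ratio below 1. This step needs no distributional assumption.

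**3. Illustrative size.** The article gives no mean or SD for ISI change, so the inputs here are assumptions: normally distributed falls with mean m and SD s, and a half-point continuity correction.

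- As written: P(D ≤ 8) = Φ((8.5 − m)/s)
- Minimum fall: P(D ≥ 8) = 1 − Φ((7.5 − m)/s)

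Worked case: m = 7 (intervention), m = 2 (waiting list), s = 5.

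- As written: Φ(0.3) = 0.618 and Φ(1.3) = 0.903. Odds ratio = (0.618/0.382) / (0.903/0.097) ≈ 0.17.
- Minimum fall: 1 − Φ(0.1) = 0.460 and 1 − Φ(1.1) = 0.136. Odds ratio = (0.460/0.540) / (0.136/0.864) ≈ 5.4.

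Other assumed inputs:

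| Mean fall, intervention vs waiting list | SD | Odds ratio as written | Odds ratio with D ≥ 8 |
|---|---|---|---|
| 7 vs 2 | 5 | 0.17 | 5.4 |
| 6 vs 2 | 5 | 0.24 | 3.9 |
| 8 vs 3 | 5 | 0.18 | 5.2 |
| 4 vs 1, 6 vs 2, 8 vs 2, 9 vs 3 | 4 to 6 | 0.07 to 0.40 | 2.4 to 13.2 |

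Every case reverses.

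**The case against.** The strongest reply is that this is a slip any careful analyst would catch. The same sentence speaks of clinically relevant improvement, the outcome section gives the 8-point change, and both places cite the same source. The authors may have had in mind a change score of −8 or lower and then called it a decrease. On this view the likely harm is an ambiguous published definition, and a reversed trial result is improbable. That is fair as to likelihood. It does not repair the sentence, which states an explicit threshold and direction and leaves nothing to be filled in elsewhere.

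A second reply is that the scope is narrow. This stands: the rule serves a secondary aim. The baseline-adjusted regressions of sleep efficiency and ISI at T3, the sample size (based on sleep efficiency), the mixed model and the mediation analyses do not use it.

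A third is that the odds ratios rest on invented inputs and on an unbounded normal model, which ignores that low-scoring entrants have little room to fall. This also stands: the values show scale only. The reversal itself comes from step 2, which does not depend on them.

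Two smaller cautions apply. The outcome section calls 8 points a relevant change without saying it is the smallest one; reading it as a minimum is an inference, though the only one that makes sense for a responder rule. And a full protocol or SAP that is not shown may contain other analyses of clinical relevance.

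**Conclusion.** The concern holds. The responder rule is wrong as written: it contradicts the article's own account of the ISI and of relevant change, and nothing else in the article corrects it. Coded literally, it turns a benefit into an apparent harm, with odds ratios of about 0.07 to 0.40 where a minimum-fall rule gives about 2.4 to 13.2, over the assumed range of inputs. The direction is certain for any benefit that moves more participants past 8 points; the sizes are illustrative. It is probably a writing error and is confined to one secondary analysis. It must still be corrected, because this sentence defines a prespecified binary endpoint that cannot be used as it stands.

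**What to change.** Replace the definition in the Statistical analyses section with: clinically relevant improvement = ISI at T0 (the screening score, per Table 1) minus ISI at T3 of at least 8 points. Use that variable in the logistic regression, carry the same wording into any SAP and the analysis code, and record the correction with a date. The article was submitted while recruitment was ongoing and plans no interim analysis, so the change could be made before any outcome comparison. It costs one symbol.

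An optional addition is to report remission (T3 ISI of 0 to 7, the article's own band for absence of insomnia) beside the responder result. A participant who enters at ISI 8 can meet the corrected rule only by reaching 0, and remission would show what the rule misses in such cases. This costs one descriptive row; the core correction does not depend on it.

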### Aims and hypotheses

The objective of this trial is to evaluate the effectiveness of the online guided cognitive-behavioral therapy “i-Sleep youth” in treating insomnia in adolescents and young adults who had childhood cancer compared to a waiting-list-control condition in a 1:1 parallel-group superiority RCT. Our hypothesis is that the intervention will improve sleep efficiency (actigraphy) and insomnia severity (self-report) on the short-term compared to the control group, which is maintained on the long-term up to a year after the intervention. Furthermore, we expect that patients in the intervention group will also show improvement on other actigraphy-based sleep parameters (sleep onset latency, wake after sleep onset, total sleep time). We will also assess two non-parametric circadian rhythm parameters, in which we expect that the intervention group will show increased stability and less fragmentation of the 24-h sleep-activity rhythm. Other outcomes we hypothesize to be improved after the intervention are HR-QoL, fatigue, (perceived) cognitive functioning, and depressive and anxiety symptoms compared to the control group. We also aim to study the acceptability of the online intervention in the adolescent target group. At last, we aim to explore the treatment mechanism in this population by studying the following mediators: chronic hyperarousal (defined as chronic distress) and disrupted daytime rhythm (napping). These mediating treatment factors were found in CBT-I for adult insomnia populations [41] and might also be mediating factors in treating insomnia after childhood cancer (higher chronic distress and disrupted rhythm due to being ill).

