### Assessments

The outcomes will be evaluated at baseline (T0), 3 months (T3), and 6 months (T6) after randomization. Patients in the intervention will additionally be assessed at 12 months (T12). See Table 1 for an overview of assessments. Acceptability of i-Sleep will be measured following the intervention. All self-report questionnaires will be offered through a secure website, www.hetklikt.nu. This secure internet environment is in use in patient care as well as in pediatric (oncology) care in the Netherlands [42, 43]. Paper questionnaires will be available upon request to the participants. The baseline choice of modality (paper-pencil or online) will be retained for all time points.

**Table 1 Tab1:** Study outcome measurements and time points

Measurement	Instrument	Nr. of items	Time-points			
			Baseline (T0-months)	Post treatment (T3 months)	Follow-up T6 months	Follow-up T12* months

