**Secondary outcomes:**						
Sleep parameters: TST, TTB, SOL, WASO, napping	Actigraph and sleep log		X	X	X	X
Circadian rhythm parameters: Fragmentation (IV) and intradaily stability (IS)	Actigraph and sleep log		X	X	X	X
Health-Related (HR) quality of life	PedsQL - teens 13–18 years - young adult 19–30 years	23	X	X	X	X
Fatigue	CIS	20	X	X	X	X
Depressive and anxiety symptoms	HADS	14	X	X	X	X
Perceived cognitive functioning	Peds-PCF-SF	10	X	X	X	X
Chronic stress	CSQ-CA	19	X		X	X
General questionnaire	Pain Sleep medication use	2	X	X	X	X
Intervention feedback	Satisfaction questionnaire, adherence	20		X*/X**		

Notes.*only intervention-condition, **at 9 months for control-condition. *TST* total sleep time, *TTB* total time in bed, *SOL* sleep onset latency, *WASO* wake after sleep onset, *ISI* Insomnia Severity Index, *CIS* Checklist Individual Strength, *HADS* Hospital Anxiety and Depression Scale, *Peds-PCFSF* Peds Perceived Cognitive functioning Short Form, *CSQ-CA* Chronic Stress Questionnaire for Childs and Adolescents

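### Chronic stress is a planned mediator of the T3 effect, but Table 1 schedules no chronic stress questionnaire at T3

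*Protocol article*

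**What the plan says.** Under Statistical analyses, the protocol article states: "Mediation analyses at T3 are performed with the regression-based PROCESS macro". It then names the mediators and outcomes: the "potential mediational effect of chronic stress and napping on treatment effectivity on SE and ISI at T3 is tested".

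Aims and hypotheses introduces the same two mediators, equating hyperarousal with chronic distress and daytime rhythm disruption with napping. The aim is worded as exploratory, comes last in the list, and ranks neither mediator above the other.

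Self-report questionnaires gives one instrument for chronic distress, the CSQ-CA. It has 17 items and is scored from 17 to 68, "in which a higher score indicates more distress in the past 3 months".

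Table 1 lists the CSQ-CA with 19 items and marks it at T0, T6 and T12. The T3 cell is empty.

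**The concern.** The article fixes both the analysis and the measurement schedule, and for this mediator they do not fit together. This is not a detail that a statistical analysis plan could supply later, because no plan can create scores that were not collected.

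What is at stake is one of the two named routes for exploring how the treatment works. If the conflict stays, the analyst must either drop chronic stress without a stated rule or substitute the T6 score. The second choice would present as a mediator something measured after the outcome it is meant to explain.

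**Working it through.** No sample-size or power arithmetic bears on this point. The check sets the schedule against the analysis.

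**1. Columns of Table 1.** The time points are, in order: "Baseline (T0-months) Post treatment (T3 months) Follow-up T6 months Follow-up T12* months".

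**2. The CSQ-CA row against a complete row.** Read as running text, the CSQ-CA row is "Chronic stress CSQ-CA 19 X X X": an item count and three marks. A complete row is "Perceived cognitive functioning Peds-PCF-SF 10 X X X X": an item count and four marks. In the table layout the gap in the CSQ-CA row lies between the T0 and T6 marks, that is, at T3. Table 1 has 11 rows (2 primary, 9 secondary). The other 10 all carry a mark in the T3 column, so the gap is specific to the CSQ-CA.

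**3. What the T3 mediation analysis needs.**

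| Variable | Role | Scheduled at | Available at T3? |
|---|---|---|---|
| SE | outcome | T0, T3, T6, T12 | yes |
| ISI | outcome | screening, T3, T6, T12 | yes |
| Napping | mediator | T0, T3, T6, T12 | yes |
| Chronic stress (CSQ-CA) | mediator | T0, T6, T12 | no |

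**4. Can another CSQ-CA score stand in?** An indirect effect is the product a × b, where a is the effect of treatment on the mediator and b is the effect of the mediator on the outcome given treatment.

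- *T0 score.* Randomisation follows the baseline assessment (Recruitment and randomization). Treatment cannot affect this score, so a = 0 by design and a × b = 0 whatever b is.
- *T6 score.* The recall is 3 months, so the window runs from month 6 − 3 = 3 to month 6. The outcome is measured at month 3. The intervention starts directly after randomisation and lasts 5–8 weeks, so it ends before that window opens (3 months is about 13 weeks; 13 − 8 = 5 weeks at the least). The mediator would follow its outcome.
- *T12 score.* This is later still, and only the intervention arm is assessed then, so a cannot be estimated.

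**5. Can imputation fill the gap?** The article plans to impute missing data. With the schedule as printed, the T3 score is observed in 0 of 70 participants. The data then hold no information on how T3 chronic stress relates to arm or to the T3 outcomes, and imputed values would reflect only the imputation model's assumptions.

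**6. Is a time-consistent alternative already scheduled?** CSQ-CA, SE and ISI are all marked at T6, and the waiting-list arm is offered treatment only after 6 months. A T6 mediator with T6 outcomes can therefore be analysed in both arms. Mediator and outcome would come from the same wave, and the question would move from the post-treatment effect to the 6-month effect.

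**The case against.** The strongest reply is that the empty cell may be a slip in the table. The Assessments section says in general terms that outcomes are measured at baseline, 3 and 6 months, with no exception for the CSQ-CA. The same row disagrees with the text on the number of items. Table 1 and the text also differ elsewhere: pain and sleep medication are marked at baseline in the table, while the text names only T3, T6 and T12. This stands as a reason not to claim that T3 scores were never collected. It does not remove the conflict, because no specific statement places the CSQ-CA at T3.

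Three stronger readings are tempting, and the article does not support them.

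- *The main mechanism hypothesis is untestable.* The aim is exploratory, neither mediator is called the main one, and napping is measured at T3.
- *The napping analysis fails too, because napping comes from the same actigraphy week as SE.* Same-wave measurement limits causal interpretation, but it contradicts nothing in the plan, which claims no time order. The timing of the ISI relative to that week is not given.
- *The main mediation model must become a T3 mediator with a T6 outcome.* That model has a better time order and is feasible, but it answers a different question. The conflict does not require it.

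It is also fair to say that adding the questionnaire may come late. Inclusion began in January 2019 and completion is expected in September 2021. The article does not say which visit defines completion. If it is the last T6 visit, the last randomisation falls by about March 2021 and the last T3 visit by about June 2021. If it is the last T12 visit, these become about September and December 2020. Many T3 visits, possibly all, may already be past.

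**Conclusion.** The point holds in a limited form. The chronic-stress half of the T3 mediation analysis cannot be run from the schedule in Table 1: one of two mediators has no T3 measurement, and neither the T0 nor the T6 score can replace it in a T3 analysis. The napping half, the primary comparison of SE and ISI at T3, and the sample size are unaffected.

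This rests on Table 1 being right as printed. If the empty cell is a misprint, the analysis can be run and the error is in the table. In both cases the article contradicts itself and needs correcting. Because the aim is exploratory and no primary conclusion depends on it, this should be fixed but is not critical to the trial.

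**What to change.** First establish whether the CSQ-CA is given at T3.

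- **If it is,** correct the T3 cell in Table 1. Nothing else in the mediation plan has to change.
- **If it is not,** choose one of these and state it before the data are analysed:
  1. Add the CSQ-CA to the T3 package in both arms for participants who have not reached T3, and report chronic-stress mediation only in those with a T3 score.
  2. Restate the chronic-stress analysis as exploratory at T6 (T6 CSQ-CA with T6 SE and ISI, controls still untreated), and acknowledge that mediator and outcome share a wave.
  3. Drop the T3 chronic-stress claim and keep napping.

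If T3 scores exist, a model of the T3 mediator on the T6 outcome is an optional addition.

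At the same time, correct the CSQ-CA item count: 19 in Table 1, against 17 items and a range of 17–68 in the text.

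Cost: option 1 needs a minor amendment and a few minutes per participant for 17–19 items in an existing online package. It yields partial mediator data, possibly from few participants. Options 2 and 3 need only a change of wording. Option 2 gives up the post-treatment time point for this mediator, and option 3 gives up the mediator.
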